**Figure 1 F1:**
[figure not shown]
Experimental paradigm of proposed study.

The first task, used during weeks 1 and 2, will present children with an image of an imaginary animal in a pastoral environment, and will ask them to make inferences about the creature's survival habits with regard to food, protection, and movement based on its appearance and the environment depicted. The second task, presented during weeks 3 and 4, depicts a girder and beam bridge made from square blocks. The abutments and piers are of unequal widths and are spaced unequally. Children will be asked about structural changes that would allow the bridge to support more weight. The third task, presented during weeks 5 and 6, depicts a ramp with a tennis or golf ball that could roll down the ramp. The length, degree of incline and material used on the surface of the ramp are shown to be adjustable. The children will then be asked to determine how the ramp parameters could be set to maximize the speed of a ball rolling down the ramp. The tasks are depicted in Figure 1.

In week one, prior to the solo phase, children will undergo training, in which the rules and mechanics of the tasks are explained and they will be guided through describing claims (what they think) and evidence (why they think that). The training is neither recorded nor timed and children are encouraged to ask any questions that they have about the experiment. After the training, during which fNIRS capping will also be carried out, fNIRS recording will begin and a first baseline recorded, during which the children will be asked to look at a white crosshair on a black screen for 60 seconds to determine resting brain activity. A second baseline will be collected before the collaborative phase of the game, and the mean of the two baselines will serve as the resting brain activity of each child.

While 176 dyads will engage in the phases described above, a small number of dyads will serve as a control. These children will engage only in solo work, and in a report to the teacher each week, with a pre-test and post-test as above, in order to differentiate between the impact on learning gains of simply engaging in the task and that of collaborating on that task. These tasks, annotation schemes and performance metrics, have been successfully used in both a child-child and child-VP longitudinal study with 7- to 8-year-olds (Finkelstein, 2018; Cassell, 2022), and have been successfully pilot-tested with 5–6 year-olds.

Because of the complexity of recruitment for longitudinal studies, and particularly those using neuroscientific methods with children, we will start by collecting data with 9–10-year-old dyads, and expect to analyze and publish the results from that work while collecting data from other age groups.

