Specifically, in the first, solo, phase the children will be asked to describe out loud as much evidence as they can muster for claims they are making. While this kind of task may sound too scientific for 5–6 year old children, a significant body of literature describes children's ability to do just this, albeit without necessarily using the words “hypothesis” or “evidence” (Sodian et al., 1991; Ruffman et al., 1993). Indeed, requesting scientific thinking of this sort is a common style of educational activity for the entire age group. If the participants are still generating answers at 8 min they will be encouraged to wrap up, and after 10 min they will be stopped.

Next the children will be invited to collaborate by sharing their ideas with the other child in the dyad, in order to come up with a final list of claims and evidence for those claims that they will later present to an experimenter.

After the collaboration phase, the children will engage in a social phase, where they will be asked to chat with one another in free discussion for 8–10 min while the experimenters “get their paperwork together”.

After the social phase, we will turn off the children's cameras and ask them to self-report their feelings of closeness to the other child in two ways: first by rating their level of preferred closeness to the other child in the dyad, using a well-validated preferred closeness scale for children (Strayer and Roberts, 1997), and then by completing their feelings of closeness using the “Inclusion of Other in Self” (IOS) scale (Aron et al., 1992; adapted for children by Rabinowitch and Knafo-Noam, 2015). They will then present their task results to an experimenter located locally in each of the two venues, for no more than 8–10 min. The experimenter will give no feedback other than continuation markers such as “uh huh”. This phase will serve to assess the children's learning gains after each week. Figure 1 summarizes the experimental paradigm.

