For each dyad, we will obtain IBS values for each 30 second epoch and each ROI pair. We will also compute the average IBS across each 8–10 min phase of the experiment. In total, we will thereby obtain IBS values for each dyad, from each ROI, for the entire phase and for each 30-second epoch within that phase. To best capture the IBS evoked by social interaction, we normalize the values of the social phase by computing a Z-score, i.e., removing the average value of the solo phase and dividing by the standard deviation. This process is repeated for each dyad. To compare the difference between phases, then, we run a general linear model (GLM). Normalized IBS values are entered as the dependent variable with interactive phases (i.e., collaboration and discussion) and the interaction effect of ROIs (six per dyad) as fixed factors. To assess whether the observed neural activity is most likely due to exchanges between the children, as opposed to being primarily driven by the content of the task, we will also generate random pairings by calculating IBS with false dyads (the child's time-series paired to the time-series of another child coming from a different dyad during the same phase). We will create multiple such random pairs to generate the distribution of IBS expected under the null hypothesis (H0) (Nguyen et al., 2021a). The values of the actual real pairs will then be compared to these H0 distributions, thus providing an empirical *p*-value. An example of this analysis is illustrated for the feasibility study in Figure 5B. We will also generate a more conservative intra-pair comparison based on temporally shuffled behavior. In this case, the participants stay the same but the epochs are randomized to generate false dyads (Ayrolles et al., 2021).

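### The solo control differs from the collaborating dyads in who hears its weekly report and, on the plain reading, in task time, so it does not isolate collaboration

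*Protocol article*

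**What the plan says.** The control is described in one short paragraph of Section 4.2 (Task description), after Figure 1. It opens "While 176 dyads will engage in the phases described above" and continues that "a small number of dyads will serve as a control". Of the control children it says "These children will engage only in solo work, and in a report to the teacher each week". They also take a pre-test and a post-test. The stated purpose is "in order to differentiate between the impact on learning gains of simply engaging in the task and that of collaborating on that task".

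For the main dyads, Section 4.2 sets out this sequence:

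- **Solo phase.** Children still working are prompted to finish at 8 min, and "after 10 min they will be stopped".
- **Collaboration phase.** The pair shares ideas on the same task, "in order to come up with a final list of claims and evidence for those claims that they will later present to an experimenter".
- **Social phase.** Free discussion for 8–10 min.
- **Weekly report.** This goes to a local experimenter: "The experimenter will give no feedback other than continuation markers such as" a brief acknowledgement.

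Section 5.5 (Educational performance) confirms that the weekly report goes to the local experimenter and is the performance metric for that week. It adds that the pre-test and post-test measure gain over the 6 weeks and are given by the experimenter at each venue. For phase length, Section 5.2.2 says: "We will also compute the average IBS across each 8–10 min phase of the experiment".

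**The concern.** A control that is meant to separate collaboration from task practice should differ from the main sample in collaboration and as little else as possible. As described, two further differences come with it.

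**Who hears the weekly report.** This report is an outcome. Section 4.2 uses it to assess learning each week, and Section 6.4 counts hypotheses and evidence statements from it. A count of spoken reasoning can depend on the listener and on whether the listener prompts. The continuation-markers-only rule is stated for the experimenter and not for the teacher. Recipient coincides completely with group, so no later analysis could separate the two. Any feedback from the teacher could also act as a co-intervention during the 6 weeks.

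**How long the child works on the task.** The collaboration phase is a second period on the same task. If controls have nothing in its place, a larger gain among collaborating children could reflect longer practice instead of collaboration. Controls also have no social phase.

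Section 4.2 describes no other group for telling collaboration from practice. It also says that the 9–10-year-olds will be collected and published first, so an unmatched control would be built into the first report.

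**Working it through.** **1. Check the phase length against the plan's own figure.** Section 5.4 gives 192 to 240 rapport ratings over the two dyadic phases in 6 weeks, at one rating per 30 seconds.

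- Per phase: 8 × 2 = 16 to 10 × 2 = 20 ratings.
- Two phases: 32 to 40.
- Six weeks: 32 × 6 = 192 to 40 × 6 = 240.

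This reproduces the plan's figure exactly, so 8–10 min per dyadic phase is a sound input.

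**2. Task time over 6 weeks.** The formula is weeks × minutes of task work per week. The solo phase is taken as 8–10 min, from the phase length in Section 5.2.2 and the 10 min stop in Section 4.2.

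| Group | Per week | Over 6 weeks |
|---|---|---|
| Main dyads: solo + collaboration | 16–20 min | 96–120 min |
| Control: one solo phase (assumption A) | 8–10 min | 48–60 min |
| Control: solo work in both task slots (assumption B) | 16–20 min | 96–120 min |

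Under A the ratio is 0.50 when phases have equal length, with extremes 48/120 = 0.40 and 60/96 = 0.625. Under B it is 1.0. The article does not say which applies. A is the plain reading, because these children do solo work only and no substitute for collaboration is mentioned.

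**3. Sensitivity to a short solo phase.** The solo phase has a cap but no minimum. If it lasted only 4 min in both groups (an illustrative value), the ratio under A would be 4/(4 + 10) = 0.29 to 4/(4 + 8) = 0.33. A shorter solo phase widens the gap.

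**4. Adding the social phase.** Three phases of 8–10 min come to 144–180 min over 6 weeks for the main dyads. Under A the controls' share of that total is 1/3 with equal phase lengths.

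**5. Which outcome each difference reaches.** The pre-test and post-test named for the control are taken to be those of Section 5.5, the only place that describes them.

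| Outcome | Collected alike in both groups? | Recipient difference | Time difference (under A) |
|---|---|---|---|
| Weekly read-out | No: teacher against experimenter | Direct | Direct |
| Pre-test to post-test gain | Yes: experimenter at each venue | Only indirect, through any teacher feedback | Direct |

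**The case against.** The strongest reply has four parts.

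- **The time gap is inferred.** The article gives no duration for the control's solo work, and a condensed article may leave a small group's timetable to the full protocol. This stands. A reader might take half the task time as a fact of the design, but the text supports it only as a conditional figure.
- **The 6-week gain is measured alike.** The venue experimenter gives the pre-test and post-test. This also stands. A reader might conclude that the control comparison as a whole is uninterpretable. That does not follow, because only the weekly read-outs are directly affected by the change of recipient.
- **Teacher may be loose wording for experimenter.** This is possible, since every other mention of the weekly report names an experimenter. Nothing in the document shows that the teacher prompts the children. Even so, the passages then disagree with Section 5.5 and with the rest of Section 4.2, and need to be reconciled.
- **The control is a side comparison.** None of the six claims rests on it, no analysis in Section 6 uses it, and it lies outside the power analysis in Section 4.1. This stands and limits the severity.

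A reader might also infer that control dyads will be picked by convenience. The article is silent on allocation, and silence in a condensed article is no evidence of that.

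Finally, solo work against solo work plus collaboration plus chat is a legitimate contrast of packages. It is not the contrast that Section 4.2 says it wants.

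**Conclusion.** The concern holds at moderate severity. As written, the control differs from the main dyads in more than collaboration, which its stated purpose does not allow.

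The recipient difference is explicit in the text. It makes the weekly comparison of hypothesis and evidence counts confounded with who elicits the report. Its size cannot be estimated from the document.

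The time difference rests on one assumption: that the control does a single solo phase per week with nothing in place of collaboration. It is then 48–60 against 96–120 min over 6 weeks (ratio 0.50, range 0.40–0.625 for phases of 8–10 min), and it would bear directly on the pre-test to post-test gain. If solo work fills both slots, this part disappears. The missing social phase is a further difference on the same reading.

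The inter-brain synchrony, rapport and performance analyses within the 176 dyads are not affected.

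**What to change.** In the control paragraph of Section 4.2:

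1. Replace the report to the teacher with the same weekly read-out to the local experimenter, under the same continuation-markers-only rule. Experimenters are already at each venue, so this is a wording change.
2. State the control's solo working time and set it equal to the solo plus collaboration time of the main dyads. On the plain reading this adds about 8–10 min per control session, or 48–60 min over 6 weeks. It may tax the youngest children, whose short attention span Section 4.2 itself notes.
3. If time is not matched, limit the stated conclusion to a contrast of solo work with the whole package of solo work, collaboration and social chat, and drop the attribution to collaboration alone. Even with time matched, acknowledge that controls have no social phase.

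Settle this before the 9–10-year-old data are collected, since that group is to be published first.

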## 5 Data collection

### 5.1 fNIRS data acquisition

Functional NIRS data will be collected using two NIRx NIRSport2 machines. Each child will be connected to a separate machine with 16 sources and 16 detectors, using a sampling rate of 7.81 Hz, and wavelengths of 760 nm and 850 nm. The imaging montage of the fNIRS caps (pictured in Figure 2B) covers the 3 areas implicated in social interaction described in prior work above: the left and right PFC, STS, and TPJ. Eight short channels (8 mm source-detector separation, illustrated in Figure 2B) will be used to address systemic physiological artifacts (Wyser et al., 2020). Neural signals will be recorded using the NIRx Aurora and Hyperscan software packages, which automatically synchronize the recording from both NIRSport 2 machines via an *ad hoc* network. Because children may vary in head size, even within one age group, optodes that are destined to be placed in the same ROI may in fact capture data from a different region. Improved precision in channel localization will therefore be addressed by pinpointing the locations of the channels for each child in terms of the MNI coordinates, through digitization of fNIRS optode locations, as detailed by Hu et al. (2020). This method facilitates accurate spatial mapping of neural activation across participants.

### 5.2 fNIRS data pre-processing

For each subject, raw data will be visually inspected for evidence of artifacts that would result in poor data quality. Pre-processing will be carried out by MNE-NIRS, a dedicated Python library for pre-processing fNIRS data (Luke et al., 2021). To further enhance data quality, for each source-detector pair, the impact of systemic physiological factors will be attenuated by performing short-channel regression using the temporally embedded Canonical Correlation Analysis (von Lühmann et al., 2020). Raw intensity values will be converted into optical density values and then motion-corrected using temporal derivative distribution repair (Fishburn et al., 2019). The scalp coupling index (SCI), a measure of signal strength between the optodes and the scalp (Pollonini et al., 2014), will then be calculated for each of the 42 channels for the entire experiment. Any channel with an SCI value lower than 0.8 will be excluded from subsequent analysis (Pollonini et al., 2016). For the subsequent dyadic neural synchrony calculations (described further below), only shared channels with sufficient SCI will be used. Remaining data will then be converted into hemoglobin concentration values using the modified Beer-Lambert law (Baker et al., 2014). Data will be filtered in order to remove heart rate and respiration artifacts by applying a band-pass filter between 0.01 and 0.5 Hz (Yücel et al., 2021). Both oxygenated hemoglobin (HbO) and deoxygenated hemoglobin (HbR) will be analyzed, as HbO exhibits greater sensitivity to changes in cerebral blood flow (Jiang et al., 2012), while NIRS data acquired during verbal communication is most accurately represented by the HbR signal (Zhang et al., 2017), since speaking can influence end-tidal CO2 blood levels (Scholkmann et al., 2013).

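### In the order listed in 5.2, systemic physiology is regressed out before the scalp coupling index is calculated, which can push well-coupled channels below the 0.8 exclusion limit

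*Protocol article*

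**What the plan says.** Section 5.1 provides eight short channels that "will be used to address systemic physiological artifacts". Section 5.2 then gives the pre-processing in this order:

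1. Visual inspection of the raw data.
2. Short-channel regression, for each source-detector pair: systemic physiology is to be "attenuated by performing short-channel regression using the temporally embedded Canonical Correlation Analysis".
3. Optical density and motion correction: "Raw intensity values will be converted into optical density values and then motion-corrected using temporal derivative distribution repair".
4. SCI, which "will then be calculated for each of the 42 channels for the entire experiment".
5. Exclusion: "Any channel with an SCI value lower than 0.8 will be excluded from subsequent analysis". For the dyadic synchrony calculations, "only shared channels with sufficient SCI will be used".
6. Conversion to haemoglobin concentration by the modified Beer-Lambert law.
7. Filtering: "Data will be filtered in order to remove heart rate and respiration artifacts by applying a band-pass filter between 0.01 and 0.5 Hz".

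Nothing in 5.2 says that SCI is computed on data that have not yet been regressed.

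**The concern.** SCI is the correlation between the two wavelengths within the cardiac frequency band. An optode in good contact with the scalp records the same pulse at both wavelengths, so the correlation is high. A poorly coupled one records mostly unrelated noise. The pulse is also a systemic physiological signal, which is what short-channel regression is there to attenuate. If the regression comes first, the shared signal shrinks while wavelength-specific noise remains, and SCI falls for a reason unrelated to contact. The 0.8 limit then partly measures how well the regression worked. Channels where it works best would be the most exposed.

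The exclusion is absolute, covers the whole experiment, and applies to a dyad if either child fails. Inter-brain synchrony (IBS) in the six regions of interest (5.2.2) is built from the channels that survive, and IBS enters the analyses of most of the claims in section 6.

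**Working it through.** **Inputs from the article.** SCI limit 0.8, 42 channels, and the order of steps (5.2). Sampling rate 7.81 Hz and eight short channels (5.1). The Nyquist frequency is 7.81/2 = 3.905 Hz, so the cardiac band is recorded and available to SCI.

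**Assumptions not in the article.** The article describes SCI only as an indicator of signal strength at the scalp. Its cardiac basis is taken here from the definition of the statistic. The true SCI of a channel, s, and the share of cardiac-band power removed by the regression, r, are not given, so ranges are shown. The article states no figure that could be reproduced first.

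**Model.** In the cardiac band, let s be the share of variance common to both wavelengths and 1 − s the wavelength-specific noise. Removing a share r of the common power gives

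SCI after regression = s(1 − r) / [s(1 − r) + (1 − s)].

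Example: s = 0.95 and r = 80% gives 0.19 / (0.19 + 0.05) = 0.79.

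| True SCI | r = 50% | r = 80% | r = 90% | r = 95% |
|---|---|---|---|---|
| 0.90 | 0.82 | 0.64 | 0.47 | 0.31 |
| 0.95 | 0.90 | 0.79 | 0.66 | 0.49 |

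**Removal at which a channel reaches 0.8.** Setting the expression to 0.8 gives s(1 − r) = 4(1 − s), so r = 1 − 4(1 − s)/s.

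- s = 0.90: 1 − 0.40/0.90 = 56%
- s = 0.95: 1 − 0.20/0.95 = 79%
- s = 0.98: 1 − 0.08/0.98 = 92%

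**Simulation.** Ten minutes at 7.81 Hz were simulated, with eight short channels at two wavelengths, a heart rate near 1.35 Hz and a phase lag of 0.6 rad between short and long channels. SCI was computed at 0.7–2.5 Hz. Cardiac-to-noise power ratios were 10, 20 and 50 in the long channel and 2, 10 and 50 in the short channels, with ten runs per setting. Ordinary least squares stood in for the canonical correlation method, either without time lags or with lags of ±3 samples to mimic temporal embedding.

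| Power ratio, long channel | Mean SCI before regression | After, no lags | After, lags ±3 samples |
|---|---|---|---|
| 10 | 0.91 | 0.76 | 0.01–0.18 |
| 20 | 0.95 | 0.86 | 0.02–0.30 |
| 50 | 0.98 | 0.93–0.94 | 0.07–0.51 |

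Before regression every simulated channel passes 0.8. With lagged regressors every one fails. Without lags only the channels with a ratio of 10 fail. The simulated short channels carry the same pulse as the long ones apart from the phase lag, which favours removal. The lagged column therefore shows that the mechanism can be strong. It does not forecast losses in this study.

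**Compounding.** If a share p of channels passes in each child, independently, the share usable for the dyad is p².

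**The case against.** The strongest reply is that the order is inferred. The sequence words in 5.2 begin with the optical density sentence. The regression sentence stands before that chain, has no such word, and can be read as a general statement of purpose. The next sentence also starts from raw intensity values, which would no longer be raw if the regression had been run. A condensed article need not list software steps in execution order. This stands in part: the code may well run in another order, so the loss is conditional. It does not clear the text, because the only order given puts the regression ahead of the exclusion rule, and no sentence places it elsewhere.

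Second, the article speaks of attenuating systemic factors, not eliminating them, and nothing in it shows how much cardiac power is removed. That also stands. A channel with true SCI 0.98 survives until about 92% is removed, and the unlagged simulation leaves the two better-coupled cases above 0.8.

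Third, heavy exclusion would be noticed. The 9–10-year-olds are collected and analysed first (4.2), and section 9 reports good data quality in all five feasibility dyads. However, the article does not say that the feasibility data went through this pipeline, and moderate losses would be harder to attribute to step order.

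A reader might also infer that motion correction before SCI is an error. The article states that order explicitly, and nothing examined here shows it to be wrong.

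**Conclusion.** The point holds in conditional form. Followed as listed, 5.2 attenuates the signal that SCI depends on and then applies a hard limit of 0.8 to the result. Under the assumed values, channels with true SCI 0.90, 0.95 and 0.98 fail once about 56%, 79% and 92% of cardiac-band power is gone. This rests on the definition of SCI, on assumed coupling and removal shares, and on the listed order being the order run.

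A reader might go further and conclude that good channels will be lost, or that whole regions of interest will be emptied. The article does not support that: the removal share is unknown, the number of channels lost cannot be computed, and the order is listed without being expressly fixed. What is established is that the text permits, and on its face describes, a sequence in which the exclusion rule may not mean what it is meant to mean. It is worth correcting before the first age group is analysed.

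**What to change.** State in 5.2 that raw intensity is first converted to optical density, that SCI and the 0.8 exclusion are computed on data to which short-channel regression has not yet been applied, and that the regression follows the exclusion. Motion correction may stay where it is relative to SCI. No step, threshold or equipment changes, so the cost is a reordering of the pipeline. If the code already works this way, one clarifying sentence is enough. Any data already processed in the listed order would need to be reprocessed from the raw recordings.
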